#### Follow-up data collection

The disease-specific data, including tumour stage, pathological subtypes of MOGCTs, tumour markers’ value, surgical options and chemotherapy response, etc, will further be recorded in detail. The patients need to routinely follow-up in outpatient before each chemotherapy cycle. The frequency of outpatient follow-up after finishing chemotherapy is set as follows: every 3 months within 3 years after treatment and every 6 months between 3 and 5 years after treatment. Additional follow-up will be provided in case of special conditions, such as severe chemotherapy side effects or tumour recurrence. A telephone follow-up will be a supplementary option for those patients who follow-up in local hospitals or miss the appointment day. Importantly, the patients’ smoking status, whether they receive oxygen therapy, and/or chest radiation before or during the treatment will be recorded in detail due to these factors may have a synergised effect with bleomycin.

During each follow-up, the patients will need to report the oncology outcomes, pulmonary function, QoL, menstrual conditions and fertility outcomes for childbearing patients with the desire for fertility. The interval between bleomycin-containing chemotherapy and the onset of lung injury will be exactly recorded during the trial. The QoL assessment will be based on the general conditions and self-report questionnaires listed as follows.

The privacy of patients will be rigorously protected throughout the whole study process. Any statistical analysis or publications of data can only be presented in an anonymisation format.

#### Validated questionnaires used in the trial

QoL will be mainly assessed by the Functional Assessment of Cancer Therapy Scale General (FACT-G).^23^ Other questionnaires include the Insomnia Severity Index (ISI),^24^ the International Physical Activity Questionnaire,^25^ Peripheral Neurotoxicity Questionnaire (GOG-NTX).^26^ The FACT-G is a symptomatic scale including 12 items that can evaluate patients' symptoms, chemotherapy AEs, sexual and hormonal situations, etc. Similarly, ISI includes seven items to assess the quality of sleep and the severity of insomnia. IPAG shows validation in measuring overall physical activity and its frequency and intensity. GOG-NTX uses 11 items to describe peripheral nerve disorders, such as numbness, discomfort, arthralgia, deep sensitivity problems and walking disorders. The detailed description has also been discussed in a previous study.^27^ A combination of these questionnaires can help demonstrate the life status of MOGCT patients after treatment.

### Outcomes

#### Primary outcomes

The primary outcome of the study is the declined degree of FVC in MOGCT patients who receive BEP chemotherapy revealed by respiratory function test. The secondary outcomes are the decline of other pulmonary function indices (FEV1; FVC pred% and DLCO), the safety of nintedanib treatment, oncological and fertility outcomes, and QoL in MOGCTs patients.

The safety assessment of nintedanib is measured by patients’ vital signs, auxiliary examinations and AEs. The auxiliary examinations include blood tests (routine analysis, liver and kidney function, etc), urine and stool examinations. We will record any AE during the treatment and follow-up period. The definition and classification of AEs based on the CTCAE5.0. Treatment will be continued in case of grade 1 or tolerable grade 2 AEs, and temporary termination of treatment will be applied in case of the first occurrence of intolerable grade 2 or grade 3 AEs until recovery to grade 0–1 or grade 2 AEs. However, permanent termination of nintedanib medication will be considered on the second time of intolerable grade 2 or grade 3 AEs, no matter the previous toxicities or newly identified toxicities.

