## Introduction

Malignant ovarian germ cell tumours (MOGCTs) are heterogeneous non-epithelial ovarian malignant tumours that originate from the abnormal differentiation and malignant transformation of primordial germ cells of embryonic gonads. MOGCTs are rare and only account for about 3% of all ovarian malignancies, with an estimated incidence of 0.4/100 000 women years and mostly affected patients about 20 years.^1 2^ It is estimated that approximately 60%–70% of MOGCTs patients are diagnosed with International Federation of Gynecology and Obstetrics (FIGO) stage I, and only less than 5% are with FIGO stage IV diseases on initial treatment, therefore, the prognosis of MOGCTs patients is usually satisfactory.^1 3^

Currently, the standard treatment for MOGCTs patients can be a combination of surgery and adjuvant chemotherapy (bleomycin, etoposide and cisplatin, BEP regimen) based on tumour stage and/or grade, while fertility-sparing surgery is always recommended in childbearing or young patients.^4 5^ Bleomycin is the crucial and irreplaceable regimen for chemotherapy in MOGCTs.^6^ However, the toxicities associated with bleomycin including acute and later-onset pulmonary toxicity have limited the dose of the regimen, in terms of treatment efficacy and have decreased the quality of life (QoL) in these young patients.^7^ The risk of pulmonary fibrosis is an important adverse effect (AEs) of bleomycin, and it has been reported that pulmonary toxicity induced by bleomycin occurred in 6.8%–46% of patients, with bleomycin-related mortality of about 3%–5%.^8^ Other AEs are less common, such as fever, hypersensitivity and organising pneumonitis.^9^

Tumour relapse usually occurs within 2 years after treatment in MOGCTs patients.^10^ Although chemotherapy after relapse can achieve a complete remission rate of about 75%, about one-third of advanced MOGCTs patients may experience recurrence or chemotherapy resistance in a short period, resulting in poor survival outcomes.^7 11^ Relapsed MOGCTs are usually not curable partly due to intolerance to bleomycin or not having enough therapeutic doses of bleomycin, whereas other chemotherapy regimens are not effective.^12^

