## Methods and analysis

### Study design

This is a prospective, randomised, double-blinded, placebo-controlled clinical trial that was registered at the Chinese Clinical Trial Registry on 14 April 2023 (ChiCTR2300070492). It has been approved by the Ethics Committee of Peking Union Medical College Hospital and will be conducted in accordance with the Declaration of Helsinki and strictly follow the latest Consolidated Standards of Reporting Trials recommendations,^21^ Standard Protocol Items: Recommendations for Interventional Trials statement^22^ (online supplemental table 1). For all patients who will participate in this study, written informed consent will be obtained before treatment.

10.1136/bmjopen-2023-074963.supp2Supplementary data

A total of 128 participants diagnosed with MOGCTs treated with BEP chemotherapy will be enrolled in the trial. The total screening and enrolling period will last for about 2.5 years in estimation, and they will be followed up for at least 1 year (up to 5 years) after treatment. The enrolment is planned to start on 1 October 2023 and end on 1 April 2026. The participants will be randomised and assigned to either the intervention group or the placebo group in a 1:1 ratio using a central randomisation system. In addition to standard adjuvant chemotherapy, they will be given nintedanib (150 mg) or placebo in granule form twice a day before chemotherapy till 1 month after the last cycle of chemotherapy.

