### Participants

The inclusion criteria are listed as follows:

Newly diagnosed MOGCTs patients who will be treated with BEP chemotherapy or bleomycin-based chemotherapy.Age between 14 and 40 years.Pulmonary function test can be completed.FVC≥45% of normal predicted value and DLCO≥60% of normal predicted value.Patients who agree and sign the written informed consent, and with good compliance.

Patients who meet the following criteria will be excluded:

Patients with pre-existing interstitial lung disease.Patients with severe medical diseases, severely impaired liver function (transaminase increased to 2.5 times the upper limit of normal) and severely impaired renal function (creatinine clearance rate <30 mL/min).Combined with other reproductive system malignant tumours.Complicated with deep vein thrombosis, pulmonary embolism, myocardial infarction, cerebral infarction and other diseases.Combined with other diseases requiring long-term hormone therapy.Patients with chronic obstructive pulmonary disease or pulmonary hypertension that influence pulmonary function.Patients who are considered not suitable to be enrolled by researchers.

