### Sample size calculation

This study adopted a non-inferiority clinical trial design, and the sample size was calculated by using the sample size calculation website (https://sample-size.net). Based on the decline in lung function of patients treated with bleomycin at 1 year in the literature and the improvement in pulmonary function with nintedanib,^17 28–30^ we set the decline of FVC in the placebo group as over 8%. Based on the efficacy of nintedanib in the study of pulmonary fibrosis patients,^16^ we set the decline of FVC in the nintedanib group as 4%. Using a non-inferiority cut-off value of 10%, a one-sided α value of 0.025, and the test power of 0.09, we calculate the sample size of a single group as 53. Considering the group set a 1:1 ratio in two groups and 10% of the dropout cases during the trial, at least 116 patients will need to be included (online supplemental figure 1). Moreover, we presume that no more than 10% of the enrolled MOGCT patients may be unable to continue to receive bleomycin-based chemotherapy due to the pulmonary fibrosis, we will recruit additional 10% patients (12 patients) to better conduct this trial. Therefore, we plan to include at least 128 patients in this trial.

10.1136/bmjopen-2023-074963.supp1Supplementary data

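### The primary FVC change is not referenced to predicted values in a trial that enrols from age 14; lung growth does not bias the arm comparison but costs some precision, which covariate adjustment could largely recover

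*Protocol article*

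**What the plan says.** The Primary outcomes section of the protocol article states: "The primary outcome of the study is the declined degree of FVC in MOGCT patients who receive BEP chemotherapy revealed by respiratory function test". It gives neither a unit nor a time point. The next sentence sets FVC % predicted apart from the primary: "The secondary outcomes are the decline of other pulmonary function indices (FEV1; FVC pred% and DLCO". The Abstract and the Objective make the same split.

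On age and growth:
- Participants: "Age between 14 and 40 years". The Introduction says of the disease that it "mostly affected patients about 20 years". Recruitment and consent provide for juveniles through their guardians.
- The predicted scale is already used for eligibility: "FVC≥45% of normal predicted value and DLCO≥60% of normal predicted value".
- Sample size calculation takes its planning horizon from the literature: "Based on the decline in lung function of patients treated with bleomycin at 1 year in the literature". It sets declines of over 8% (placebo) and 4% (nintedanib), without saying what they are percentages of.
- Study design: "they will be followed up for at least 1 year (up to 5 years) after treatment".

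Data management and statistical analysis says that two-group comparisons are chosen by data type. The only multivariable models it names are Cox and logistic regression. The article does not mention growth, or adjustment for age or height.

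**The concern.** In a patient who is still growing, expected FVC rises over the interval. Her observed change is therefore bleomycin injury minus growth, and the trial wants to measure the first term. Percent change from her own baseline does not help, because it contains the same growth. Only a value referenced to age and height, or an analysis that accounts for them, addresses it.

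Three things are at stake:
- The decline reported in each arm is too small if adolescents contribute, and the placebo arm may miss its assumed 8% for a reason unrelated to the drug.
- Growing and non-growing patients mixed in one arm make the change score more variable.
- If one arm happens to receive more adolescents, the arm difference shifts by that imbalance times the growth.

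**Working it through.** **Inputs from the protocol article (Sample size calculation):** 53 patients per group; declines of 8% and 4%, so a difference of 4 points.

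**Assumptions, because the documents give none of these:** SD of FVC change 8 points; share still growing f = 0.30; growth g of 1, 3 or 5% of FVC over the interval; growth independent of arm; a two-sided 5% comparison of means. The stated 53 cannot be reproduced on a continuous scale, because no SD is given. It is taken as it stands, and the point does not depend on it.

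**Step 1, expected values.** Growth lowers the observed mean decline in each arm by f × g. At g = 1 this is 0.3: 8 becomes 7.7 and 4 becomes 3.7. At g = 5 it is 1.5: 8 becomes 6.5 and 4 becomes 2.5. The difference stays at 4.

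**Step 2, variance.** Variance = 64 + f(1 − f)g² = 64 + 0.21g².

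**Step 3, power.** Power = Φ(4 / (SD × √(2/53)) − 1.96).

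| g | Variance | SD | Power |
|---|---|---|---|
| 0 | 64.00 | 8.00 | 73.0% |
| 1% | 64.21 | 8.01 | 72.9% |
| 3% | 65.89 | 8.12 | 71.8% |
| 5% | 69.25 | 8.32 | 69.7% |

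The loss runs from about 0.1 to about 3 points of power.

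**Step 4, chance imbalance.** The standard error of the difference in share growing is √(2 × 0.21 / 53) = 0.089. An imbalance of that size moves the arm difference by 0.089 × g: about 0.09 points at g = 1 and 0.45 points at g = 5, against a planned difference of 4. This is the Step 2 variance seen from another side, not an additional loss.

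**Step 5, sensitivity to the assumptions.** If the SD is instead chosen so that 53 per group gives 90% power for a 4-point difference, it is 4 × √(53/2) / (1.960 + 1.282) = 6.35. With 10% of patients gaining 2%, power is 89.7%. With 40% gaining 8%, it is 78.8%. That lower end is an extreme scenario for a 1-year horizon and a disease centred near age 20.

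**The case against.** The strongest reply is that this is a design preference. FVC as primary with FVC % predicted as a prespecified secondary outcome is coherent, the growth-referenced measure will be reported anyway, and a statistical analysis plan that is not shown may already adjust for age. Change in % predicted has its own weakness: it depends on the reference equations and on re-measured height. Using the predicted scale at entry compares one measurement with a norm. It does not oblige the trial to use that scale for change.

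Most of this stands, and it argues against replacing the primary outcome. It does not remove the point. The article itself describes how groups will be compared, and nothing there takes growth out of the primary outcome.

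Three stronger readings are tempting and are not supported:
- *Growth biases the treatment effect.* Allocation is 1:1 and randomised, so additive growth cancels in expectation (Step 1).
- *The primary is raw FVC in millilitres.* The article does not say so. Its planning figures are percentages, and percent of own baseline remains possible. What is clear is only that the primary is not % predicted.
- *Growth removes a large part of the effect on patients with a 10% decline.* With SD 8 and g = 5, the arm difference in that share does fall from 17 to 11 points, but only among growing patients. With 30% growing, the whole-trial figure goes from 17.5 to 15.4 points (0.7 × 17.5 + 0.3 × 10.6), or to 17.1 at g = 1. The protocol defines no such responder outcome; its 10% is a non-inferiority margin.

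**Conclusion.** The point holds as a modest loss of precision. The primary change score retains lung growth in patients enrolled from age 14, and the analysis described in the article does not account for it. The expected arm difference is unbiased. Within-arm declines are understated, by 0.3 to 1.5 points if 30% of patients gain 1–5%, and power falls by about 0.1 to 3 points if the SD is 8. All of these rest on assumed values for SD, share growing and growth rate. With a typical age of about 20, growing patients may be a minority and the effect may lie at the low end. It is worth acting on because the remedy costs almost nothing, not because the trial's conclusion is threatened.

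**What to change.** Keep FVC as the primary outcome. In Data management and statistical analysis, replace the two-group comparison chosen by data type, for this outcome, with a linear model of FVC change on treatment, adjusted for baseline FVC, age and baseline height. Name change in FVC % predicted as the prespecified sensitivity analysis of the primary outcome, with one fixed set of reference equations and height re-measured in adolescents. State the scale of the primary change and its time point in the same amendment.

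The cost is slightly more analysis work and a height measurement at pulmonary function visits. FVC % predicted is already an outcome, so baseline age and height are needed in any case. The adjustment recovers growth only as far as age and height predict it, so the losses shown above are the most it can win back.

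Making FVC % predicted the primary is optional and costs more. The 8%, 4% and 10% figures in Sample size calculation would have to be restated on that scale, the result would depend on the reference equations, and a change after enrolment has begun could look like outcome switching.

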#### Study group assignment

After the exclusion and inclusion process, we will perform the concealed study group assignment based on the central randomisation system. An independent statistician will generate a randomisation sequence for all the eligible MOGCTs patients. The patients will be randomly allocated to either nintedanib (experimental) or placebo (control) groups. For all the MOGCT patients enrolled in this trial, a standard treatment, namely comprehensive fertility-sparing surgical staging, or radical surgical staging plus BEP chemotherapy for 3–4 cycles, in accordance with the ESMO guidelines,^5^ no matter whether they are assigned to which group. In addition to standard treatment, patients allocated to the nintedanib group will be given oral nintedanib 150 mg two times per day before the first cycle of BEP chemotherapy until 1 month after the last cycle of BEP chemotherapy. Accordingly, patients in the control group will be given an oral placebo one tablet per time, two times per day before the first cycle of BEP chemotherapy until 1 month after the last cycle of BEP chemotherapy. The nintedanib and placebo will be provided by the study team and the appearance will be the same, without identifiable labels or packaging. The patients will be requested to record the medication and return the packaging to researchers after treatment. The flow chart (figure 1) shows the simplified procedure of group allocation, interventions and outcomes assessment.

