#### Termination of therapy (nintedanib or placebo)

The planned end of treatment (till 1 month after the last cycle of BEP chemotherapy).Termination of treatment due to severe AEs.Withdrawal of written informed consent.

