#### Harms

The safety of nintedanib in treating IPF has been confirmed in previous clinical trials.^16^ The AEs are usually mild and tolerable. The most common AEs of nintedanib therapy are as follows (incidence ≥5%): diarrhoea, anorexia, sickness, vomiting, abdominal pain, headache, elevated liver enzyme, weight loss or hypertension. Other rare AEs reported in previous research include haemorrhage, gastrointestinal perforation, elevated bilirubin levels and cardiac toxicity. However, currently, there has been limited data on the safety of nintedanib in MOGCT patients receiving bleomycin-based chemotherapy. Therefore, unpredicted AEs may be found during this trial, and all the AEs observed during the study period will be treated according to the clinical practice. Especially, for MOGCT patients receiving bleomycin-based chemotherapy, the benefit of prevention of bleomycin-induced pulmonary toxicities would be greater than the risk and the harms of nintedanib itself.

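### The restart threshold after a study-drug pause omits the word tolerable before grade 2, so drug may resume when a grade 3 AE has fallen only to an intolerable grade 2

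*Protocol article*

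**What the plan says.** The dosing rule for adverse events is in the Protocol article under Outcomes, Primary outcomes, after the statement "The definition and classification of AEs based on the CTCAE5.0". It has four parts.

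- Continue: "Treatment will be continued in case of grade 1 or tolerable grade 2 AEs".
- Pause and restart, in the same sentence: drug is stopped temporarily at the "first occurrence of intolerable grade 2 or grade 3 AEs until recovery to grade 0–1 or grade 2 AEs".
- Permanent stop, in the next sentence: "permanent termination of nintedanib medication will be considered on the second time of intolerable grade 2 or grade 3 AEs", whether the toxicity is the earlier one or a new one.

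The section on termination of therapy gives severe adverse events as one reason to end study treatment. It sets no level at which paused drug may be restarted.

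**The concern.** CTCAE supplies the grade. The protocol adds its own split within grade 2, between events the patient can tolerate and events the patient cannot, and that split decides whether drug continues or is paused. The restart threshold uses grade 2 without the split. Taken literally, a patient could go back on study drug while still having toxicity at a level that the rule treats as a reason to withhold it.

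At stake is the safe and uniform handling of blinded study drug in patients aged 14 to 40 who are receiving BEP. The Harms section acknowledges that safety data for nintedanib in this population are limited. One site may restart at any grade 2 and another may wait until the event is tolerable, and both could say that they followed the text.

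**Working it through.** The plan states no figure on this point and no arithmetic applies. The check sets the parts of the rule side by side.

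**Step 1: where the qualifier appears.**

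| Part of the rule | How grade 2 is described |
|---|---|
| Continue | tolerable |
| Pause | intolerable |
| Restart | no qualifier |
| Permanent stop | intolerable |

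Three of the four parts carry the qualifier. The restart part alone does not.

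**Step 2: what each level permits, for a patient paused for a grade 3 event.**

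| Level now | Reason to pause? | Restart allowed as written? | Restart allowed with the word added? |
|---|---|---|---|
| Grade 0 | no | yes | yes |
| Grade 1 | no | yes | yes |
| Tolerable grade 2 | no | yes | yes |
| Intolerable grade 2 | yes | yes | no |
| Grade 3 | yes | no | no |

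Intolerable grade 2 is the only level that is both a reason to pause and an allowed restart level. With the word added, no level is both. Every level above grade 0 at which drug may restart is then also a level at which drug may continue.

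**Step 3: the two ways into a pause.**

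- *Paused for grade 3.* A fall to intolerable grade 2 is a real improvement and ends at grade 2. It meets the restart wording in full, so the gap is open here.
- *Paused for intolerable grade 2.* The text requires recovery. An event that has not changed has not recovered, so it is at least doubtful that the restart condition is met. The conclusion does not rely on this route.

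**Step 4: a paired reading.** The threshold might be meant in pairs: a grade 2 event must fall to grade 0–1, and a grade 3 event to grade 2. That closes the second route entirely. It leaves the first open, because intolerable grade 2 is still grade 2.

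**Step 5: is the qualifier supplied elsewhere?** No. The termination section gives no restart level. The Harms section says that adverse events will be treated according to clinical practice, which sets no threshold.

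**The case against.** The strongest reply is that the sentence, read as a whole, has one sensible meaning. Its opening clause allows drug to continue only at grade 1 or tolerable grade 2, so a clinician who restarted at an intolerable level would be outside that clause at once. The word recovery points the same way, clinical practice governs the treatment of adverse events, and a condensed article may leave detailed dose-modification instructions to the full protocol. On this view it is a wording slip whose meaning can be recovered.

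Much of that stands. It probably is a slip, and the intended meaning can be inferred. But the article does not leave the rule to another document: it states it, and states one part differently from the other three. Inference is a weak basis for a dosing rule when the literal text gives a different answer for the same patient.

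Three stronger readings are tempting, and the document does not support them.

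- *Every intolerable grade 2 event qualifies for restart at the moment it triggers the pause.* This ignores the requirement of recovery.
- *Early restart leads to an early permanent stop.* The stop is only to be considered, and only on a second occasion. Nothing says that the residual phase of the first event counts as a second one.
- *The stop rule applies to the nintedanib arm only, because it names nintedanib alone.* The two products look the same, "the appearance will be the same, without identifiable labels or packaging", and the termination section is headed for both products. Blinded staff could not apply an arm-specific rule, so this is loose wording and not a second defect.

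**Conclusion.** The point holds in a limited form. As written, study drug may be resumed when a grade 3 event has fallen to an intolerable grade 2, a level that the same sentence gives as a reason to pause. The conclusion rests on two things: the literal wording, and the assumption that an event can improve from grade 3 to grade 2 and still be intolerable. The protocol's own split within grade 2 allows for that.

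The size is small and cannot be put as a count. The gap matters only for patients paused for a grade 3 event that passes through an intolerable grade 2. The Harms section lists common nintedanib events, beginning "The most common AEs of nintedanib therapy are as follows (incidence ≥5%): diarrhoea, anorexia, sickness, vomiting, abdominal pain", but not by grade or tolerability, so no number of affected patients can be derived. A reader might infer some bias in the FVC comparison from uneven exposure to drug. The article gives no basis for that and none is claimed. This is a minor correction to a safety rule.

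**What to change.** In the safety paragraph under Primary outcomes, insert *tolerable* before *grade 2* in the restart threshold, so that a pause lasts until recovery to grade 0–1 or tolerable grade 2. This matches the continue rule at the start of the same sentence. Leave the pause and permanent-stop rules as they are.

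The cost is one added word, with no extra patients, visits, data or analysis. Some pauses will last longer, because drug stays off until the event is tolerable. The continue rule already implies that.
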